### Cost-effectiveness analysis

The clinical effectiveness analysis will be complemented by an economic evaluation that will estimate the cost-effectiveness of each intervention versus screening alone. Alcohol use disorders and associated problems generate high costs in health care and in society more widely, including costs to the criminal justice and social care systems. The incremental cost effectiveness of the two interventions versus screening will thus be assessed from a societal perspective that will account for resource savings beyond the NHS.

The costs of screening and of delivering the two interventions will be estimated by prospectively monitoring resource inputs to each arm of the trial, including training, valued using standard methods [36]. Effects on NHS and non-NHS costs will be estimated from information gathered on patient contact with primary care, secondary care, specialist health services, social services and criminal justice. These will be assessed retrospectively using the CSRI tool. Service use will be valued using local costs where possible supplemented by national sources and information from previous alcohol studies [34,37,38].

Cost effectiveness will be assessed in terms of the incremental net health benefit (NHB), which converts costs and Quality Adjusted Life Years (QALYs) gained, as estimated from EQ-5D-5 L scores and UK population utility values, into a single monetary value. Differences in QALYs will be estimated from the ‘area under the utility curve’. Both one-way and multi-way sensitivity analyses will be carried out to explore our basic assumptions. Non-parametric bootstrapping will be used to investigate joint uncertainty in costs and effects via cost effectiveness acceptability curves.

Three secondary analyses will be undertaken. The first will adopt a narrower NHS perspective including only costs and savings relating to the NHS and personal social services. This will us to compare the NHB with other interventions assessed using the narrower perspective recommended by the National Institute for Health and Care Excellence (NICE) for the economic evaluation of NHS interventions. The second will compare total societal costs with decreased alcohol consumption for the high-risk group. The third will compare total societal costs with the proportion of the low-risk group maintaining moderate alcohol use.

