### Objectives of the study

Two linked randomised controlled trials will be conducted. Both trials will evaluate the effectiveness and cost-effectiveness of BI intervention strategies compared with screening alone. One trial will focus on high-risk adolescent drinkers attending Emergency Departments and the other will focus on those identified as low-risk or abstinent from alcohol. In both trials our primary outcome measure will be quantity of alcohol consumed at 12 months after randomisation.

Secondary objectives for each study include:To identify key predictors of recruitment to the trials.To explore the process of treatment through key psychological constructs that may lead to further refinement of the proposed interventions.To identify prognostic factors that improve outcome.To explore interactions between participant factors, setting factors, treatment allocation and outcomes.

Our primary (null) hypothesis is similar for both trials: Personalised Feedback and Brief Advice (PFBA) and Personalised Feedback plus electronic Brief Intervention (eBI) are no more effective than screening alone in reducing alcohol consumed at 12 months after randomisation measured by the Time-Line Follow-Back 28-day version. Our secondary (null) hypothesis relating to economics states that PFBA and eBI are no more cost-effective than screening alone.

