### Screening and baseline assessment

After consent has been given, by parent or guardian if appropriate, the participant will complete a screening and baseline assessment. All participants scoring 3 or more on the AUDIT-C questionnaire (high-risk drinkers) will be randomised between three groups – two intervention groups and the control group receiving screening alone. Of those scoring less than 3 on the AUDIT-C (low-risk drinkers or abstainers) one in three will be randomly selected to continue with the study and then randomised between three analogous groups. Participants who score less than 3 but are not selected for the study will be thanked for their participation, given a £5 voucher and returned to the care of ED staff.

The screening and baseline assessment includes demographic information and contact details, health and lifestyle questions, the AUDIT-C [29], questions 19, 21 and 22 from the European School survey Project on Alcohol and other Drugs (ESPAD) [5], the Strengths and Difficulties Questionnaire [30], the EQ-5D-5 L [31], and a short service use questionnaire [32]. This takes approximately 10 minutes to complete.

To simplify and enhance data collection we have developed an electronic interface which will only show relevant questions to participants. To maximise completion rates this interface uses an attractive graphic interface. Participants can skip questions or withdraw consent at any stage of the process. All of the instruments have been designed and validated for those aged 14 to 17. The screening and baseline assessment will be conducted by trained researchers with experience of working with adolescents; all researchers will have completed enhanced Disclosure and Barring Service checks in advance. All information given by participants will be treated in confidence.

In total 1,500 participants will be recruited into the trials, 750 high-risk alcohol users and 750 low-risk alcohol users. Participants will be randomized with equal probability, stratified by centre, between a screening only control group and one of the two interventions – a single session of face­to­face Personalised Feedback and Brief Advice (PFBA) or Personalised Feedback plus a smartphone or web-based brief intervention (eBI). All participants will be eligible to receive treatment as usual in addition to any trial intervention.

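### All stated economic comparisons are against screening alone, so for three mutually exclusive options the plan should add a joint three-arm analysis and correct the description of net health benefit

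*Protocol article*

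**What the plan says.** The Screening and baseline assessment section describes "two intervention groups and the control group receiving screening alone" and adds: "Participants will be randomized with equal probability, stratified by centre". A participant receives one of the three.

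The economic null hypothesis, in the Abstract and under Objectives of the study, is that "PFBA and eBI are no more cost-effective than screening alone". The Cost-effectiveness analysis section sets the contrast in the same way twice. It will "estimate the cost-effectiveness of each intervention versus screening alone", and "The incremental cost effectiveness of the two interventions versus screening will thus be assessed from a societal perspective".

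The main measure in that section is incremental net health benefit, which is said to convert costs and QALYs "into a single monetary value". Joint uncertainty is to be handled by non-parametric bootstrapping and acceptability curves. The section does not say whether the curves are pairwise or cover all three options.

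Of the three secondary analyses, one repeats the net-benefit analysis from the NHS perspective. The other two use natural units. For high-risk drinkers, "The second will compare total societal costs with decreased alcohol consumption for the high-risk group"; for low-risk participants, costs are set against the proportion who keep to moderate use. Neither has a stated monetary value per unit of effect.

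**The concern.** A commissioner choosing a policy for a given risk group picks one of three options. The decision question is therefore which of the three is best value, and how sure one can be of that. The comparator is a choice that the article makes explicitly, in the hypothesis and twice in the economic section; it is not merely a detail left out.

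Two things go unanswered if the analysis stops at the stated contrasts:

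- **Uncertainty about the choice.** The probability that an intervention beats screening is not the probability that it is the best of three. Both interventions can have a high value of the first when neither has a high value of the second.
- **The natural-unit analyses.** Without a value per unit of consumption avoided, or per participant kept at low risk, costs and effects cannot be put on one scale. An intervention can then look acceptable against screening although its extra cost over the other intervention buys very little.

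The wording on net health benefit is a separate, smaller matter. Net health benefit is measured in health units; a monetary summary is net monetary benefit. The article plans to compare its figure with those of other interventions, so the scale needs to be clear.

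**Working it through.** The article states no numerical result or target for the economic evaluation, so there is no figure of its own to reproduce here. It also gives no costs, QALYs, variances or threshold. Everything numerical below is an illustration on assumed inputs.

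**1. What the stated contrasts already deliver.** Write NHB = ΔQALY − ΔCost/λ, with λ the threshold. At any fixed λ,

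NHB(eBI vs PFBA) = NHB(eBI vs screening) − NHB(PFBA vs screening).

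So the two planned estimates rank all three options. Assume costs of 0, 50 and 150 and QALYs of 0, 0.008 and 0.010 for screening, PFBA and eBI, with λ = 20,000:

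- PFBA vs screening: 0.008 − 50/20,000 = 0.0055 QALYs
- eBI vs screening: 0.010 − 150/20,000 = 0.0025 QALYs

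PFBA ranks first without any direct comparison.

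**2. What ratios against screening would hide in the same example.**

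- PFBA vs screening: 50/0.008 = 6,250
- eBI vs screening: 150/0.010 = 15,000
- eBI vs PFBA: (150 − 50)/(0.010 − 0.008) = 50,000

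Both ratios against screening are below 20,000, but the step from PFBA to eBI is well above it. In the QALY analysis, net benefit shows this. In the natural-unit analyses no value per unit of effect is stated, so no net benefit is available and only the eBI-versus-PFBA increment would show it.

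**3. Uncertainty.** Let the two incremental net benefits against screening be normal with equal standard errors (SE). With independent arms, each of variance s², each difference has variance 2s² and their covariance is the control arm's s², so the correlation is s²/2s² = 0.5. Equal allocation makes equal variances a reasonable starting assumption. With means m₁ and m₂ in SE units:

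- pairwise probability = Φ(mᵢ)
- screening is best with probability P(both differences ≤ 0)
- intervention i is best with probability P(NBᵢ > 0 and NBᵢ > NBⱼ)

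| m (PFBA, eBI) | Pairwise vs screening | Best: screening / PFBA / eBI |
|---|---|---|
| 0.8, 0.8 | 79%, 79% | 9.5% / 45% / 45% |
| 1.0, 0.8 | 84%, 79% | 8% / 54% / 39% |
| 1.0, 1.0 | 84%, 84% | 6% / 47% / 47% |
| 1.0, 2.0 | 84%, 98% | 1% / 15% / 83% |
| 2.0, 2.0 | 98%, 98% | under 1% / 50% / 50% |

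For the first row, Φ(0.8) = 0.788, P(both ≤ 0) = 0.095, and by symmetry each intervention is best with probability (1 − 0.095)/2 = 0.45. Some rows do not add to exactly 100% because of rounding. The fourth row is the clearest: PFBA beats screening with probability 84% but is the best option with probability 15%.

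**4. The label.** Net monetary benefit = λ × NHB. In the example, 20,000 × 0.0055 = 110 for PFBA and 20,000 × 0.0025 = 50 for eBI. The order is the same on both scales; only the unit differs.

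**The case against.** The strongest reply is that the analysis matches its hypothesis. That hypothesis asks about each intervention against screening, and the economic section estimates this. A pairwise probability of 79% is a correct answer to that question. This stands, and it is why the contrasts with screening should stay.

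A reader might go further and infer that the plan cannot show which option is best. The article does not support that: net benefit against a common comparator ranks the three at a given threshold.

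A reader might also infer that the plan specifies pairwise curves and cost-per-effect ratios. It specifies neither. The curves' form is not stated, and three-option curves from the same bootstrap are not excluded. For the natural-unit analyses the article says only that costs will be compared with effects. If cost and effect differences against screening are reported separately, the eBI-versus-PFBA point estimates can be had by subtraction, though their joint uncertainty cannot.

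Finally, this is a condensed article, and a health economics plan that is not shown may contain the joint analysis. That limits the weight of the point. It does not remove it, because the article names its comparator repeatedly and a joint analysis would have to go beyond the contrasts stated.

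**Conclusion.** The point holds in a limited form. Every economic comparison stated is with screening alone, although the three arms are alternatives. The ranking by expected net benefit is safe. What is not provided is the probability that each option is the most cost-effective, if the curves follow the stated contrasts, and an eBI-versus-PFBA increment in the two natural-unit secondary analyses.

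The size depends on assumed inputs. Over the cases shown, an intervention with a pairwise probability of 79% to 98% has a probability of being best of between 15% and 83%. These are properties of three-option decisions under normality, equal standard errors and a correlation of 0.5; they are not predictions for this trial. Nor does the article claim that its curves give the probability of being best; the risk is that they are read so.

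The description of net health benefit as a monetary value is a plain wording error. It is minor, because both scales order the options identically at a fixed threshold.

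**What to change.** Keep the two contrasts with screening as the test of the stated hypothesis. Add to the Cost-effectiveness analysis section, for each trial:

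- Resample all three arms within the same bootstrap and present acceptability curves giving the probability that each of screening, PFBA and eBI is the most cost-effective.
- Report fully incremental results for the QALY and natural-unit analyses. Order the options by cost, identify those that are dominated or extendedly dominated, and give the increments between successive remaining options. Report the eBI-versus-PFBA differences in cost and effect in any case.
- Either name the summary net monetary benefit, or keep net health benefit and express it in QALYs. State the threshold values used.

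The cost is some analysis text and slightly more programming on data and a bootstrap already planned. Sample size and data collection are unaffected. The downside is presentational: the probability shown for each intervention will look less favourable than in a comparison with screening alone.

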### Qualitative analysis

To explore acceptability of trial tools and processes to young people presenting at emergency departments we shall use semi-structured interviews to study: issues relating to consent by young people aged 14–17 years; alcohol screening; the baseline questionnaire and the burden on emergency care; and young person experiences of intervention delivery. A purposive sample of participants will be selected from the pool of participants in the two linked trials for interviews about the experience and acceptability of receiving the interventions. The sampling will cover the key variables of interest including: gender; ethnicity; age; level of alcohol use; area of the country (North East, Yorkshire and Humber or London), allocated intervention and whether it was delivered. To achieve this, a sample of at least 20 young people is likely to be required. However, recruitment will continue until data saturation is deemed to have been achieved, that is no new issues or themes are arising in the interviews.

A participant information leaflet explaining the qualitative study will be sent to a sample of young people who provided consent to be contacted for interview and, when appropriate, their parents. The young people will be invited to attend a one-to-one semi-structured interview. The interviews will be conducted in a venue that is appropriate, taking consideration of confidentiality, risk assessment, participant convenience and comfort. The purpose of the interview will be explained orally to the participant before arranging interview time and date. Interviews will be audio-recorded and transcribed to support data analysis. Though the topic guide will be produced before the start of interviews, and state the aims and objectives of the study, emergent issues will be explored as they arise.

Data will be subjected to framework analysis, which is appropriate for qualitative health research with objectives linked to quantitative investigation. This analytic strategy is characterised by an approach more deductive than inductive, in which analysis is structured around given themes so findings have detailed relevance to applied research questions. Based on interview notes and review of the interview recordings, important or recurrent themes in interviewees’ responses will be identified. These will be combined with a list of key themes of research interest derived from the aims and objectives of the study. All transcripts will be repeatedly read and coded within this framework of prior headings. Data coded under each heading will be reviewed to produce a detailed description, and revised through the course of analysis to take account of all material under that heading. Finally the descriptions of headings within the framework will be compared and the relationships between them elaborated to provide a consistent interpretation of the dataset as a whole. Analysis will continue throughout the process of data collection, and will be discussed within the subgroup of the research team tasked with managing the qualitative study. This analytic process will assist in the identification of emerging themes and enhance credibility of the thematic framework and interpretation.

## Discussion

This protocol represents an innovative and ambitious programme of work evaluating the use of novel interventions to address alcohol use in adolescent populations. The study addresses both effectiveness and cost-effectiveness and is designed to provide evidence of what works in reducing at-risk drinking in this population in addition to how to reduce the progression from low to high risk drinking.

## Ethics and confidentiality

The study has been granted ethical approval by the National Research Ethics Service London – Fulham (Ref num 14/LO/0721). There are no anticipated risks in relation to either treatment. There is no documented evidence of adverse events arising from any of the proposed interventions.

All trial data will be identified using a unique trial identification number. No personally identifiable information will be held beyond the final 12-month follow up. Analytical datasets will not contain any patient identifiable information. Anonymised data will be retained for a period of 60 months.
